**4.Materials and methods:**

**Subject selection**

40 sequential patients, both males and females, diagnosed with COVID -19 and admitted to hospital as an inpatient, requiring oxygen therapy with radiological evidence of pneumonia will be recruited, 21 years of age or older, with no upper age limit (particularly as the elderly are more at risk of an increased mortality). Whilst the Chinese data suggested that males were at higher risk of increased severity than females, the primary aim of the study is to show efficacy and therefore stratification by gender will not be undertaken.

All subjects SARS-CoV-2 positive on oxygen therapy and radiological evidence of pneumonia will be offered the opportunity of entering into the clinical trial

***Patient population***

Number of subjects planned to be randomised: 40

Number of subjects expected to complete the trial: 40

SARS-CoV-2 positive patients on oxygen therapy and radiological evidence of pneumonia will have the study explained and informed consent will be undertaken at the bedside. Whilst this study is particularly addressing those patients who are English or Arabic speakers, this will not preclude those who have limited language ability in English/Arabic and a translation service will be provided. Patients will then be assessed for exclusion criteria of the study and following randomization then treatment will be instituted

**Inclusion Criteria**

1. COVID-19 diagnosis
2. Hypoxia, (Oxygen saturation of less than or equal 92% or PO2 < 60mmHg on ABG) and patient requiring oxygen therapy
3. Evidence of infiltrates on Chest Xray or CT scan

2. Able to give informed consent

3. Patients between the ages of 21 and above with no upper age.

**Exclusion criteria**

1. Patients with mild disease not requiring oxygen therapy
2. Patients with normal CXR & CT scan
3. Patients requiring ventilatory support
4. Patients with a history of allergy to plasma, sodium citrate or methylene blue, or those with a history of autoimmune disease or selective IGA deficiency.

**5. Randomisation**

The study will randomise the patients to one of 2 groups randomised by computer. The number of patients in each group will be the same and they will have an equal chance of being in either arm of the study. Randomisation code will be provided by RCSI Bahrain to be administered in the local environment.

**6.Withdrawal of Subjects**

**Once the plasma transfusion is given then it will not be possible to withdraw medication, and if the patient chooses to withdraw from the study their clinical data will still be included in the intention to treat analysis undertaken on study evaluation.**

**7.Data and Specimen Management and Quality control and quality assurance**

Patients will be assessed clinically, and their vital signs and progress will be documented in the clinical notes and in the clinical report form

Should there be any missing data then missing values will be reported in the baseline table but won’t be considered in the analysis.

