**Outcomes**
Primary outcome is 1) Requirement for invasive ventilation
Secondary outcomes: 1) Time to viral clearance (through the use of CT values) 2) Improvement in biomarkers 3) Radiological Improvement 4) Mortality rate

**Identification of suitable plasma donors among patients recovered from COVID-19**.

Patients who have recovered from COVID-19 and have been discharged from hospital will be approached to see if they will volunteer to be donors

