**2: Daily recording in case report form for 10 days or until discharge**

- blood pressure, temperature, respiratory rate
- Oxygen flow rate and oxygen device for oxygen saturation
- Full blood count(Hb, WBC, Neutrophil count, Neutrophil percent (%),Lymphocyte count, Lymphocyte percent (%),Platelets) , Biochemical profile(Na, K, Urea, Creatinine, LDH), Liver function tests(ALT,AST,ALP,GGT), CRP, PCT, LDH, Troponin, Ferritin, D-Dimer, BNP, lactate
- Date of plasma infusion
- Amount of plasma infusion
- Adverse Event or Adverse Reaction
- Patient’s current medications
- Date of Intubation
- Ventilator Setting if on ventilator

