**3: Intermittent recording in case report form for 10 day or until discharge**

- Chest Xray 1 day after completion of plasma therapy or standard treatment and on Discharge
- ABG and PaO2 values after completion of plasma therapy or standard treatment on day 1,2,3 and then every 3 days and on discharge
- SARS-CoV-2 Swab PCR with CT Value , day 1 and 3 after plasma transfusion or standard treatment, every 7 days, and on discharge

*Criteria for discontinuation of the study*.

The study will be discontinued based on any adverse reactions such as transfusion reactions or may be withdrawn by the Ministry of Health decision on safety, or if any superior drug/intervention has been identified and is available

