**10.Statistical Analysis**

Baseline continuously distributed data will be presented as means and standard deviations unless the data is non-normal in which case the data median (25th/75th centiles) will be determined; categorical data by n (%). Given randomisation to treatment, baselines will not compared statistically (10-12). Intention to treat analysis will be undertaken. Within-group differences will be shown for each treatment group separately by a mean and a standard deviation (SD). Between-group comparisons will be performed using Student’s t testing if the data is normally distributed, and non-parametric testing if it is not. For all statistical analyses, a two-tailed P <0.05 will be considered to indicate statistical significance. Time to event analysis and logistic regression will be used to analyse outcomes. Statistical analysis will be performed using the STATA statistical computer package (StataCorp. 2013. Stata Statistical Software: Release 13. College Station, TX: StataCorp LP, USA).

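### The available-case rule in Section 7 is not reconciled with intention to treat, and makes late biomarker comparisons conditional on being alive and still in hospital

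*Protocol*

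**What the plan says.** Section 7 of the protocol (Data and Specimen Management) has one sentence on missing data. It is triggered by any missing data and says that "missing values will be reported in the baseline table but won’t be considered in the analysis".

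Section 10 (Statistical Analysis) says "Intention to treat analysis will be undertaken". It names Student's t test or a non-parametric test for between-group comparisons, and time-to-event analysis and logistic regression for outcomes. Section 6 says of patients who withdraw that "their clinical data will still be included in the intention to treat analysis undertaken on study evaluation".

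The Study Schedule sets the recording period. Part 2 is headed "Daily recording in case report form for 10 days or until discharge" and covers vital signs, oxygen, the blood biomarkers and the date of intubation. Part 3 is headed "Intermittent recording in case report form for 10 day or until discharge" and covers chest X-ray, blood gases and PCR cycle-threshold (CT) values, each of which is also due on discharge.

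The primary outcome is "Requirement for invasive ventilation", with no time window. The secondary outcomes are time to viral clearance, biomarkers, radiology and mortality. Sections 4 and 9 expect all 40 patients to complete and regard dropout as unlikely to matter.

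**The concern.** Section 7 sets an available-case rule, while Section 10 promises a comparison of the groups as randomised. When an outcome value is missing, the protocol does not say which governs.

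Here missingness is built into the schedule and follows the patient's course. Someone who goes home on day 5 has no day-7 CRP, ferritin or D-dimer, and someone who has died has none either. If plasma works, its patients go home sooner and leave the late comparisons first, so those who remain in the plasma arm are relatively sicker.

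At stake is the pilot's product. Sections 2 and 9 say the trial is meant to supply an effect size for a definitive study, and Section 9 justifies 20 per group by the need to estimate effect size and variability. For late biomarkers, both would come from a selected subset.

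**Working it through.** **The plan's own figure.** The only sample-size figure is 20 per group: 2 × 20 = 40, which matches the 40 planned and 40 expected to complete. The protocol gives no power, effect size, SD, event rate or discharge rate, so nothing further can be reproduced. What follows is an illustration on assumed values.

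**Which outcomes lose values**

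| Outcome | Discharged alive | Died in hospital |
|---|---|---|
| Ventilation during the stay | Observed (intubation date recorded daily) | Observed |
| Mortality | Alive at discharge; adverse events followed to 30 days after the final study medication visit | Observed |
| Chest X-ray | Discharge film scheduled | No discharge film |
| PCR CT value | Discharge value scheduled | No discharge value |
| Blood gases | Discharge value scheduled; later days absent | No discharge value; later days absent |
| Daily biomarkers | Last daily record only; later days absent | Later days absent |

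The exposed comparisons are late-day biomarkers and, less so, blood gases.

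**Model for a late biomarker (assumed).** The biomarker Y has SD 1 and a true plasma effect of −0.5 SD. A severity score S, with correlation r to Y, decides discharge: a patient has gone home if S < c, where c is the control centile for a discharged fraction p. Plasma lowers the mean of S by δ. With λ(a) = φ(a)/[1 − Φ(a)], the difference among those remaining is

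−0.5 + r·[λ(c + δ) − λ(c)].

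Worked case: r = 0.7, p = 20%, δ = 0.5. Then c = −0.842, λ(−0.342) = 0.594 and λ(−0.842) = 0.350. The result is −0.5 + 0.7 × 0.244 = −0.33.

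Size of the observed benefit (SD) when the truth is 0.5:

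| r | δ | p = 20% | p = 30% | p = 40% |
|---|---|---|---|---|
| 0.5 | 0.5 | 0.38 | 0.36 | 0.34 |
| 0.7 | 0.5 | 0.33 | 0.30 | 0.28 |
| 0.8 | 0.5 | 0.30 | 0.27 | 0.25 |
| 0.5 | 0.25 | 0.44 | 0.43 | 0.42 |
| 0.7 | 0.35 | 0.39 | 0.36 | 0.35 |
| 0.8 | 0.40 | 0.35 | 0.32 | 0.30 |

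In the lower three rows plasma moves discharge only through the biomarker (δ = 0.5r). With r = 0.7, δ = 0.5 and p = 60%, the figure is 0.24. In the δ = 0.5 rows the expected numbers left, control against plasma, are 16.0 against 12.7 at p = 20% and 12.0 against 8.1 at p = 40%. At p = 60% they are 8.0 against 4.5.

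**Adding deaths.** Suppose patients above the control 90th centile of S have also died. The mean of S among those remaining, relative to its arm mean, is [φ(a) − φ(b)]/[Φ(b) − Φ(a)], where a and b are the discharge and death cut-offs measured from that mean. For r = 0.8, δ = 0.5, p = 20%, this is 0.149 in control and 0.494 in plasma. The difference is −0.5 + 0.8 × 0.345 = −0.22. At p = 30% and 40% the benefit is 0.19 and 0.17.

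**SDs.** Among those remaining, with discharge only, the SD is √{1 − r²·λ(a)[λ(a) − a]}.
- Control, r = 0.5, p = 20%: √(1 − 0.25 × 0.417) = 0.95.
- Plasma, r = 0.8, δ = 0.5, p = 40%: √(1 − 0.64 × 0.687) = 0.75.

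The SD is therefore about 0.75 to 0.95 of its true value.

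**The case against.** **The rule drops values, not patients.** A reader might infer that Section 7 removes from the trial exactly those who recovered or died. The text does not say that: a patient leaves only those comparisons for which the value is absent. The sentence sits under data management and names only the baseline table, so it could be read as covering baseline data alone. But it is triggered by any missing data and its consequence falls on the analysis, so the wider reading is the natural one. At best it is ambiguous.

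**It does not flatly contradict intention to treat.** Section 6 protects data already collected, which Section 7 does not remove. Declining to impute is also not in itself a breach, since a mixed model likewise uses only observed values. This stands. The fault is an unreconciled conflict with Section 10, made material by single-time-point tests on data that stop at discharge.

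**The primary outcome is safe.** A reader might infer that discharged patients drop out of the ventilation comparison. That would matter: with an assumed 6/20 ventilated in each arm, dropping 8 control and 11 plasma patients gives 6/12 against 6/9, moving the risk ratio from 1.00 to 1.33. But a patient discharged unventilated is an observed non-event for the stay, and a patient who dies in hospital has a known ventilation status. The documents do not support that inference.

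**Other secondary outcomes are partly protected.** Discharged patients have both scheduled follow-up films and a discharge PCR value, and viral clearance can be analysed as time to event. This stands; only patients who die lack the discharge values.

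**The size is assumed, and no late-day comparison is specified.** Both are true. A statistical analysis plan might settle the details, but the sentence at issue is a rule the protocol itself fixes.

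**Conclusion.** The concern holds in a limited form. Section 7 fixes a blanket available-case rule that is not reconciled with Section 10. Because recording ends at discharge and at death, late comparisons of serial biomarkers, and to a lesser degree blood gases, would describe only survivors still in hospital.

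The likely direction is attenuation of a true benefit, provided plasma hastens discharge. If it did not (δ = 0 in the model), discharge alone would leave the mean difference unchanged, though the SDs would still shrink. For a true 0.5 SD the observed difference is roughly 0.24 to 0.44 SD with discharge alone, and about 0.17 to 0.22 SD in the strongest-correlation case with deaths also lost. These are illustrations on assumed correlations and discharge and death rates, not estimates or bounds for this trial. Quoting only the low end would overstate the case.

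The primary outcome, mortality, and the discharge radiology and PCR values are largely unaffected for discharged patients. This should be fixed, but it concerns secondary outcomes and does not put the trial's main comparison at risk.

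**What to change.** - **Section 7:** replace the missing-data sentence, or limit it to how missing baseline values are shown in the baseline table.
- **Section 10:** state that all 40 patients are analysed in the group to which they were randomised.
- **Primary outcome:** count a patient discharged alive and unventilated as a non-event over the hospital stay.
- **Biomarkers, blood gases and CT values:** use a baseline-adjusted repeated-measures model with all observed values, including the discharge value, in place of single-day t or rank tests on whoever remains.
- **Death and discharge:** the model does not give meaning to values after death, so add a rank-based sensitivity analysis that scores death worst and discharge alive best.

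The cost is a few sentences in Sections 7 and 10 and a little more analysis work. No new data are needed if the primary outcome is defined over the hospital stay. If a fixed horizon beyond discharge is chosen instead, ventilation status after discharge is not scheduled and would need a follow-up contact.

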**8.Samples storage:**

Serum samples will be sent to the laboratory processing and storage at -80C for future cytokine and antibody analysis.

Study I.D code will be assigned for each subject on day of recruitment. Samples will be stored and linked to the study I.D code. Data will be entered by the assigned CRC or any assigned study staff and then stored using a secured data base server. Each specimen will have a code only on the tube. No name, subject I.D, date or other identifying information will be on the specimen.

The Lead PI and the researchers assigned by him will have access to the stored data/specimens. Only the Lead PI and his delegated authority working on this study will be eligible to obtain the data/specimens from the participants.

Under no circumstances will any data or specimens be uncoded. After each study visit the collected data will be entered on data entry program on secure computer, the password to this computer will only be in the custody of the assigned CRC. The location of this computer will be at the BDF. The hard copy of the data will be kept in a locked cabinet, the assigned LPI or his delegated authority, will be the only personal having the keys. The collected specimens from the subject each session will be coded immediately then put in the laboratory freezer for future batch analysis.

**9.Sample Size**

There are currently no robust studies in man that would allow for a definitive power calculation and therefore this study can be considered a pilot study with the outcome of providing an effect size that would allow the powering of a definitive study. Power and sample size for pilot studies has been reviewed by Birkett and Day(9). They concluded that a minimum of 20 degrees-of-freedom was required to estimate effect size and variability and hence 20 patients per group have been included in this study; dropouts are unlikely to be an issue in this study.

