**2.Objectives**

**Primary objective**

The objective of this pilot study is to compare plasma therapy using convalescent plasma with antibody against SARS-CoV-2 to usual supportive therapy in COVID-19 patients with pneumonia and hypoxia, and to determine if the clinical course is improved. The difference between groups will allow an effect size to be determined for a definitive clinical trial

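### The degrees-of-freedom rule behind 20 per group does not establish precision for the yes/no primary outcome, so the pilot's observed difference cannot by itself size the definitive trial, and the stated aim of showing efficacy contradicts the pilot aim

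*Protocol*

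**What the plan says.** Section 9 (Sample Size) says that no definitive power calculation was possible, calls the study a pilot, and rests the number on one statement: "a minimum of 20 degrees-of-freedom was required to estimate effect size and variability and hence 20 patients per group" were included. It does not say which outcome the rule refers to, or whether the degrees of freedom are per group or pooled.

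Section 3 (Outcomes) names one primary outcome: "Primary outcome is 1) Requirement for invasive ventilation". This is a yes/no event. Biomarkers and viral CT values appear among the secondary outcomes.

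The total is fixed under Patient population ("Number of subjects planned to be randomised: 40") and the allocation in section 5 ("The number of patients in each group will be the same").

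Two aims are stated. Section 2 gives the pilot aim: "The difference between groups will allow an effect size to be determined for a definitive clinical trial". Section 9 repeats it. Section 4 (Subject selection) says instead that "the primary aim of the study is to show efficacy and therefore stratification by gender will not be undertaken". Section 10 sets a two-tailed 0.05 significance threshold for all analyses.

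**The concern.** For a continuous measure the standard deviation is unknown, and the residual degrees of freedom determine how well a pilot estimates it. A proportion has no separate variance to learn: it is p(1-p), fixed by the rate. Precision for the ventilation outcome depends on the number of patients and the event rate, and section 9 addresses neither in relation to that outcome.

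Two things are at stake. First, sections 2 and 9 tie the size of the next trial to the difference seen here, so an imprecise difference passes directly into that trial's sample size. Second, with showing efficacy written as the primary aim and a 0.05 threshold in force, a non-significant result could be read as a failed trial when it is the expected result of a small pilot.

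**Working it through.** **Inputs from the protocol.** 20 per arm, 1:1, two-sided alpha 0.05, binary primary outcome, all 40 expected to complete. **Assumptions.** The protocol gives no event rates, so control rates of 10% to 50%, each halved by treatment, are used for illustration. Differences are control minus plasma, so positive values favour plasma.

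**1. The plan's own figure.** Per-group degrees of freedom are n - 1 = 20 - 1 = 19, so 20 would need 21 per group. Pooled degrees of freedom are 2n - 2 = 2 × 20 - 2 = 38, and 20 would need only 11 per group. The stated number is one patient per group short on the first reading and above the minimum on the second. It is accepted here.

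**2. Precision and power for the primary outcome at 20 per arm.** Wald half-width = 1.96 × √[(p1(1-p1) + p2(1-p2))/20]. At 30% versus 15% this is 1.96 × √[(0.21 + 0.1275)/20] = 0.255. Power is for Fisher's exact test, found by enumerating all 21 × 21 outcomes. The last column is the normal-approximation size for 80% power.

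| Assumed rates | 95% half-width (points) | Fisher power | n per arm for 80% power |
|---|---|---|---|
| 10% vs 5% | 16 | 2% | 435 |
| 20% vs 10% | 22 | 7% | 199 |
| 30% vs 15% | 25 | 12% | 121 |
| 40% vs 20% | 28 | 19% | 82 |
| 50% vs 25% | 29 | 27% | 58 |

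By normal approximation, 80% power at 20 per arm needs a fall from 40% to about 4%, or from 50% to about 10%. At a 30% control rate, even near-total elimination of events gives only about 78% (Fisher 76%).

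**3. One pilot result.** For 6/20 versus 3/20 the Wilson intervals are 14.5% to 51.9% and 5.2% to 36.0%. Newcombe's method combines them:
- lower limit: 0.15 - √[(0.300 - 0.145)² + (0.360 - 0.150)²] = -0.111
- upper limit: 0.15 + √[(0.519 - 0.300)² + (0.150 - 0.052)²] = 0.390

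The interval runs from 11 points of harm to 39 points of benefit.

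**4. Sizing the next trial on the observed difference.** Take the truth as 30% versus 15%. The size per arm for 80% power is (1.960 + 0.842)² × [p1(1-p1) + p2(1-p2)]/(p1-p2)² = 7.849 × 0.3375/0.0225 = 118 (121 with the pooled-variance form in the table). Applying the same formula to every possible pilot result, weighted by its probability:
- the difference is zero or reversed in 16.7% of pilots, and no size can be derived in favour of plasma;
- in the remainder, the derived size per arm has a 10th centile of 22, a median of 79 and a 90th centile of 903 (25, 82 and 906 with the pooled-variance form).

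Two results show how this spread arises. Observing 9/20 versus 2/20 gives 7.849 × 0.3375/0.1225 = 22. Observing 4/20 versus 3/20 gives 7.849 × 0.2875/0.0025 = 903.

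**5. The two aims side by side.** Sections 2 and 9 describe a pilot that estimates an effect size. Section 4 describes a study whose primary aim is to show efficacy. Both cannot be primary, and the power column shows that the second is out of reach for a halving of risk at any control rate considered.

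**The case against.** A reader might infer that 20 per group does not follow from 20 degrees of freedom. The documents do not support that. The rule is worded as a minimum, 38 pooled degrees of freedom satisfy it, and 19 per group miss it by a single patient. The text is silent on which is meant, so this is loose wording and not an arithmetic error. What the cited methods paper concluded cannot be checked from the protocol, and nothing here depends on it.

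A reader might also infer that the rule is irrelevant to the whole study, or that the design delivers nothing. Neither holds. Section 10 plans means, standard deviations and t tests, and for biomarkers and CT values the estimation of variability is a sensible pilot goal. Twenty per arm does yield an effect estimate with an interval; the estimate is simply imprecise. The absence of a power calculation is not a fault either, because section 9 openly declares a pilot.

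The efficacy phrase occurs in a clause explaining why there is no stratification by gender, while the formal objective and the sample-size section both describe a pilot. That makes the correction small, but the contradiction remains.

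Finally, the spread of derived sizes comes from one assumed scenario, its median of about 79 is not extreme, and nothing in the protocol forbids a later team from using the interval. This stands as a limit on the claim: it cannot be said that the next trial would be badly sized. But sections 2 and 9 name the observed difference or effect size as the basis and do not mention its uncertainty.

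**Conclusion.** The concern holds for the primary outcome and for the wording of the aims. The degrees-of-freedom rule does not show that 20 per arm gives useful precision on invasive ventilation, and the expected 95% half-width is about 16 to 29 points over the assumed rates. Using the observed difference alone to size a definitive trial is unsupported: under 30% versus 15%, about one pilot in six shows no benefit, and the middle 80% of the other derived sizes spans roughly 22 to 903 per arm against a true need of about 118 to 121. The efficacy aim in section 4 contradicts sections 2 and 9 and has 2% to 27% power for a halved risk.

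All event rates and the halving are assumptions. The low power for a halving holds across the whole range; the figures for derived size belong to the single scenario of 30% versus 15%. The number of patients is not wrong. This is a should-fix matter of stated justification and use of results.

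**What to change.** Keep 40 patients and make three wording changes:

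- **Section 9:** limit the degrees-of-freedom rationale to the continuous outcomes and say whether it is per group or pooled. For the primary outcome, state the expected 95% confidence interval width for the ventilation risk difference over a range of assumed control rates, for example half-widths of about 16 points at 10% versus 5% up to 29 points at 50% versus 25%.
- **Section 4 (Subject selection):** replace the efficacy aim with the pilot estimation aim of section 2.
- **Sections 2 and 9:** say that the definitive trial will be sized on a minimum important difference together with the pilot's event rate and its confidence interval, and not on the observed difference alone. The interval matters because the rate is itself imprecise: 6/20 has a Wilson interval of about 15% to 52%.

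The cost is text in three sections and a less favourable justification. No patients are added, and allocation, outcomes and planned tests are unchanged.
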